### Study design

This is a randomised, multicentre, single-blind crossover superiority study of repositioning in ventilated proned patients in ICU using the BathMat vs conventional care (Fig. 1).

**Fig. 1 Fig1:**
[figure not shown]
Study flowchart

#### Study setting

The trial will be performed across at least four adult ICUs within England. This is the minimum required to ensure adequate recruitment of 30 patients within the timescale of the trial and demonstrate external validity through recruitment across centres with a range of experience in proning. The use of multiple centres also facilitates recruitment of adequate numbers of patients within the 14-month trial and allows for comparison between differences in repositioning practice, allowing generalisability of the data acquired.

#### Sample size

A sample size of 30 patients was determined from statistical analysis of the proposed trial. This is sufficient to detect a decrease in repositioning time of at least 10 min with a power of over 95%. An estimated 10-min improvement was identified via a preliminary unpublished volunteer study. This was determined to be the optimal route to estimate the approximate magnitude of time saving before the device was trialled on patients as part of the proposed clinical study.

Power calculations were carried out using Monte Carlo sampling to allow for variability in the number of repositionings per proned session and the number of proned sessions per patient. In addition to standard deviation assumptions, 2–4 repositionings per proning session were used (randomly sampled with proportions (1/5, 3/10, 1/2)) and a dropout rate of 1/3 after the first session. The repeated measurements for each patient were simulated using a correlation of 0.7 within the same treatment and 0.3 between the two treatments.

#### Blinding and randomisation

Due to the nature of the device being tested, it is only possible to perform a single-blind study to evaluate the device. Participants will be randomly assigned to be repositioned on day 1 either with BathMat or standard care with a 1:1 allocation. Randomisation will be performed using SealedEnvelope.com with a block randomisation tool stratifying by site. Block sizes will not be disclosed to ensure concealment.

Clinical staff will enrol participants and assign intervention on recruitment by using SealedEnvelope.com, either online or via text service. Only participants meeting all inclusion/exclusion criteria will be allocated to an intervention.

#### Inclusion criteria

Any sedated, ventilated patient over 18 years of age identified as requiring proning by a senior ICU clinician.

#### Exclusion criteria

Patients who are:AwakePregnantUnder guardianshipIn their first proning session in the current ICU admission who have already been repositioned 2 or more times using standard care prior to recruitment to the studyOver 200 kgUnder 150 cm and over 205 cmPatients who have already been proned using conventional methods in the current ICU admissionPatients who have broken skin on the anterior chest or abdominal wall

#### Withdrawal criteria

Participants will be withdrawn from the study if they do not supply or withdraw their consent for participation, or if their personal or nominated consultee opinion is that they would not wish to be included in the study.

## Device details

The device, shown in Figs. 2 and 3, consists of an inflatable mat for single patient use and one reusable control unit. The functionality of the control unit will be assured by the trial team at the University of Bath. There are no special storage conditions for the device.

**Fig. 2 Fig2:**
[figure not shown]
BathMat with cutaway section

**Fig. 3 Fig3:**
[figure not shown]
BathMat

### Inflatable mat

The inflatable mat, consisting of three inflatable vessels of different sizes, is pictured in Fig. 2. It is designed to be placed between the mattress and the bedsheet, underneath the patient. Direct contact between the mat and any part of the patient should be avoided. The marked upper side will have a shoulder line to indicate appropriate positioning of the superior aspect of the patient’s shoulders. A non-interchangeable connector allows connection between the mat and the control unit.

### Control unit

The control unit (Fig. 4) is used to manually control the flow of air to and from the inflatable vessel, allowing a user to inflate and deflate the vessels as required in a bespoke fashion. It has three connections: an electrical power cable for connection to a wall socket, standard medical air hosing to connect to a 4 bar medical air outlet, and bespoke hosing to connect the control device to the inflatable vessel when required. The casing has an integral carry handle and hooks for tidying of cables for storage.

**Fig. 4 Fig4:**
[figure not shown]
Control unit

The bespoke hosing, arising from the left lateral aspect of the unit, is long enough to connect to the inflatable vessel with the unit hung from the side of the patient’s bed. A non-interchangeable connector (Fig. 5) only allows connection to the appropriate ports. Clasps either side of the connector provide a secure connection between the two aspects of the device. Gentle pressure releases these clasps and allows separation of the control unit and inflatable vessel when desired. In the unlikely event of connection problems between the control unit and the mat, each trial centre will be supplied with a spare control unit and replacement hosing.

**Fig. 5 Fig5:**
[figure not shown]
Bespoke connector

The power switch is located on the left lateral wall of the control unit, marked by the universal power symbol. A power light indicates when the unit is switched on. If switched off, the control unit will not function, and no inflation is possible. There is no backup internal power source. In case of external power failure whilst inflated, the BathMat should be disconnected from the control unit to allow it to slowly deflate.

On the slanted superior aspect of the unit are the buttons to control inflation and deflation. Clearly marked to highlight which segment of the vessel they relate to, pressing each up arrow allows inflation of the relevant vessel. Pressing the down button results in deflation. If no buttons are pressed, the inflatable vessel will remain at the set inflation level.

## Training in use of device

All staff expected to be involved in repositioning will receive training in the use of the device in line with the instructions for use. This may be delivered by local or central study staff. Clinical staff will be responsible for the appropriate use of the device. Before using the device clinically, they may refresh training using a centrally produced training video or reviewing the training materials as required to ensure adherence to the instructions for use, which are also kept with the device controller at all times, with a quick reference guide should this be required by clinical staff.

Any staff receiving training in the use of the device will also receive training in the data entry requirements for assessing the primary outcome and other data only able to be recorded contemporaneously by clinical staff detailed in Tables 2 and 3. Any clinical staff using the device is required to have this training in order to use the device.

**Table 2 Tab2:** Data to be entered by clinical team after each repositioning exercise

Repositioning start time Repositioning ready time Repositioning stop time Number of staff taken to reposition Cause for any delays in repositioning Complications during repositioning Perceived ease of repositioning Perceived acceptance of use of BathMat (if used) Other comments, reasons for delay in repositioning, etc.

**Table 3 Tab3:** Repositioning complication domains

Tracheal tube blockage/displacement/extubation Infusion line kink/displacement Nasogastric tube displacement Bleeding from airway Other repositioning complication	

A training log will be kept by local site teams detailing staff trained and will be monitored centrally. Recruitment at each site will not begin until an adequate proportion of local clinical staff has received this training in order to ensure safe use of the device and appropriate data entry by clinical staff.

## Study procedures

Patients ventilated and identified as suitable for proning by the ICU consultant/senior doctor will be randomised to be repositioned whilst in the prone position with either standard care or the BathMat on a 1:1 basis. The same repositioning method will be used throughout each proning session but will alternate on subsequent proning sessions between BathMat and standard care, if proned more than once. This will account for patient-to-patient heterogeneity in individual variables such as the requirement for PPE and body mass index. A total of 30 participants will be recruited, and each participant will be involved in the study. The SPIRIT figure for the trial is shown in Fig. 6.

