## Background and rationale

Approximately 235,000 patients per year are admitted to ICU in the UK. One of the most common reasons to be admitted to an ICU is the need for respiratory support. Evidence suggests that over 16,500 ICU patients per year (7%) [1] have lung injury of significant severity that proning will be beneficial to improve both oxygenation and chances of survival. Proning describes the technique whereby sedated patients on a ventilator are turned onto their front. Once proned, patients stay on their front for 16–18 h. Depending upon the patient’s condition, this process may be repeated up to five times during an ICU stay, although during the COVID-19 pandemic, some patients were proned up to 10 times. The use of proning has been shown to reduce the risk of death by 17.4% [2]; this is one of the greatest reductions in mortality from a single intervention in intensive care medicine, and this underpins the enthusiasm of clinicians to employ the technique. Whilst proned, a patient’s head needs to be turned and their arms repositioned (hereafter termed ‘repositioning’) regularly to minimise the risk of pressure sores and nerve/organ injuries. This task requires a team of five or more staff and takes 30–60 min to perform (more if full personal protective equipment (PPE) is required).

The evidence that proning improves oxygen levels and survival rates in patients who are severely oxygen dependent in ICU is irrefutable. As such, the technique forms an essential component of national and international guidance for ICU clinicians. Complications associated with proning are well described [3]. To mitigate the risk of complications, national guidance recommends repositioning every 2–4 h. Greater awareness of the benefits of proning following the COVID-19 pandemic means that the use of the technique may be more readily employed in the post-pandemic era. This increase, in combination with the unwieldy, demanding, and far from risk-free repositioning process (described below), means there is an urgent need to explore safer and more efficient repositioning techniques.

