### Where patients are proned more than once

If a senior ICU clinician decides that more than one episode of proning is clinically indicated, the method of repositioning will alternate during each subsequent proning session as illustrated below. This illustration is intended for explanation only, and it should be highlighted that the number of times participants in the study are proned will be based solely on clinical indication and decision-making.

If proning is re-employed later in the patient’s ICU stay, the process of alternating the repositioning system will resume. For example, if a patient is proned on day 1 of their ICU admission and is randomised to standard care, and next requires proning on day 5 of the ICU stay, they will be repositioned using the BathMat on day 5, as per the table below.

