### Data collection by research team

A representative from the research team will review participants in the trial whilst the participant is in ICU throughout the period they are being proned, or the first working day afterwards if this has occurred over the weekend; once they have regained capacity; and at 3 months post discharge. They will collect patient data as detailed in Tables 4, 5 and 6 including standardised risk scoring measures used in ICU with potential relevance to our study (Waterlow, SOFA scores) [8, 9]. Data on device metrics will be obtained through discussion with clinical staff caring for the proned patient. They will ensure complete data sets are recorded through access to the clinical data entry form and spreadsheet, collect personal and nominated consultee opinions as required, and obtain patient consent. Patient notes will not be accessed by members of staff outside of those in the direct team until consent has been obtained.

**Table 4 Tab4:** Data to be collected by local research team—demographics

Patient metrics: Age, height, weight Frailty score Sequential Organ Failure Assessment (SOFA) [9] score on day 1 of proning Waterlow Pressure Ulcer Risk Assessment Scale on day 1 of proning [8] Pre-existing complications before day 1 of proning—see Table 6 ICU pressure sore risk score Medical comorbidities Diagnosis Device metrics—see Table 5 Proning complications—see Table 6

**Table 5 Tab5:** Data to be collected by local research team—device metrics (where clinical team who have used device are available)

Ease of introduction under the patient Ease of inflation/deflation Suitability of speed of inflation/deflation Ease of repositioning—head/arms Manual handling issue/concern Other comments

**Table 6 Tab6:** Data to be collected by local research team—proning complications

Pressure sore (face/chest/pelvis/knees/feet) Nerve injury (neck/arm/abdomen/leg) Blood vessel injury Skin abrasion Organ injury (liver/pancreas/genitals/ocular) Other	

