### Statistical analysis

We will test for a treatment effect using a linear mixed effects model with repositioning time as the response, fixed effects for site, sequence group assignment, and repositioning method, with random effects for individual to account for repeated measures. Analysis of the number of staff needed to carry out the repositioning procedures will take a similar approach, using a mixed effects cumulative logistic model to account for the discrete nature of the data. All tests will use the conventional 5% significance level.

No imputation or other statistical adjustments for missing data will be undertaken for these analyses. All recorded measurements of repositioning time and the number of staff needed within each proning session for the analysis, which means there is a very low chance that patients will be excluded from the analysis based on missing data. It will not be possible to tell if data on a repositioning exercise is fully missing. Whilst estimates of the treatment effect stratified by case complexity and BMI would be of interest, no sub-group analyses are planned as these would not be statistically reliable given the size of the trial.

This trial is focused on establishing efficacy in relation to the core repositioning outcome. Demonstrating efficacy is a necessary step before progressing to a larger trial that could robustly assess clinical outcomes, such as the prevention of pressure ulcers, which are relatively rare and require significantly larger sample sizes to detect with confidence. As such, this study is not powered to detect statistically significant effects in secondary outcomes, and formal hypothesis testing for these could be misleading. However, collecting and reporting detailed summary statistics will allow assessment of trends, variability, and effect sizes, which are essential for designing an appropriately powered future trial.

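### Alternation is credited with handling PPE and body mass index in general, but it does so only for stable factors in patients who receive both methods; adjusting for both would be a cheap, modest gain

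*Protocol article*

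**What the plan says.** The Study procedures section keeps one repositioning method within a proning session and switches it at the next session, if there is one. It then gives the benefit: "This will account for patient-to-patient heterogeneity in individual variables such as the requirement for PPE and body mass index". The Background states that a turn takes 30 to 60 min, and "more if full personal protective equipment (PPE) is required".

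The Sample size section assumes "a dropout rate of 1/3 after the first session", with correlations of 0.7 within and 0.3 between treatments. The example under Where patients are proned more than once has a patient proned on day 1 who "next requires proning on day 5 of the ICU stay".

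The Statistical analysis section models repositioning time with "fixed effects for site, sequence group assignment, and repositioning method" plus random effects for individual. It uses all recorded measurements, plans no imputation, and rules out subgroup analyses (BMI is one it names) because the trial is small. Table 4 lists "Patient metrics: Age, height, weight". No item in Tables 2 to 6 asks whether PPE was worn.

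**The concern.** A crossover removes a patient characteristic from the comparison only when the patient supplies data under both methods and the characteristic has not changed in between. Two groups fall outside that.

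- **Patients with one session**, about 10 of 30 on the plan's own assumption. They contribute a comparison between different patients, in which BMI and PPE need do not cancel.
- **Patients whose PPE status differs between sessions**, if there are any. Sessions may be days apart, and a change in PPE then enters the within-patient difference in full.

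The protocol presents both factors as differences that the design must deal with, and says that PPE lengthens a turn. Yet neither is in the model, and PPE is not recorded systematically. The analysis could therefore neither adjust for PPE nor show that it did not matter. The small size that argues against subgroup analyses does not argue against covariate adjustment. At stake are an overstated design claim and some avoidable variance.

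**Working it through.** **Inputs from the protocol.** "A sample size of 30 patients was determined from statistical analysis of the proposed trial"; a 10 min difference; power over 95%; one third stopping after session 1; correlations 0.7 and 0.3; 2, 3 or 4 turns per session with proportions 1/5, 3/10 and 1/2 (taken in that order). "All tests will use the conventional 5% significance level"; I take this as two-sided.

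**Assumptions.** The SD is not given (12 min is used where one value is needed). Also assumed: four sites, 40% PPE prevalence, a PPE effect of 5 to 15 min, and 0 to 20% of two-session patients changing PPE status.

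**1. The plan's own power.** Mean turns per session = 2×0.2 + 3×0.3 + 4×0.5 = 3.3. The correlations imply variance shares of 0.3 for patient, 0.7 − 0.3 = 0.4 for patient-by-method, and 0.3 residual. In units of SD²:

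- 20 two-session patients: 2(0.4 + 0.3/3.3)/20 = 0.0491
- 10 one-session patients, 5 per method: 2(0.7 + 0.3/3.3)/5 = 0.316
- weight of the one-session patients: (1/0.316)/(1/0.316 + 1/0.0491) = 0.134
- combined SE = √[1/(1/0.316 + 1/0.0491)] = 0.206 × SD

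Generalised least squares with site and sequence terms and random turn numbers gives 0.213 × SD. Power = Φ(10/SE − 1.96) is then 99.7% at SD 10, 97.4% at SD 12 and 91.8% at SD 14. It exceeds 95% up to SD = 10/[0.213 × (1.96 + 1.645)] = 13.0 min. So the stated power is attainable for SDs up to about 13 min **with** the one-third dropout and **without** covariates. With no dropout the SE would be 0.182 × SD. The one-session patients therefore cost 0.213/0.182 = 1.17, or 17% in SE, and the plan already carries that cost.

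**2. BMI.** It cancels in two-session patients, so only the part with weight 0.134 can gain. If BMI explained half of the patient-level variance, the one-session term would fall to 2(0.7909 − 0.15)/5 = 0.256. The combined variance would go from 0.0425 to 0.0412, about 3% before the cost of estimating the coefficient. The full model gives reductions of 0.1%, 0.8% and 2.2% when BMI explains 10%, 25% and 50% of patient-level variance. Removing all patient-level variance would lower the SE by only about 4%.

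**3. PPE, as part of the planned variance, SD 12.** The variance of one patient's difference between methods is 2×144×0.4909 = 141.4. If a fraction q of two-session patients change status and PPE adds g minutes, q×g² of that is due to PPE. For g = 10 and q = 0.2 the share is 20/141.4 = 14%; for g = 15 and q = 0.1 it is 22.5/141.4 = 16%. The full model, which counts the one-session patients and the cost of the extra term, gives these cuts in variance:

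| PPE effect | no change | 10% change | 20% change |
|---|---|---|---|
| 5 min | 0.2% | 1.1% | 2.0% |
| 10 min | 2.5% | 7.9% | 13.4% |
| 15 min | not possible | 20.7% | 32.8% |

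The empty cell would need a stable PPE variance of 0.4×0.6×225 = 54, more than the planned patient-level variance of 0.3×144 = 43.2. The last cell gives PPE 54/144 = 37.5% of all planned variance, which makes it a limit rather than a likely case. In every cell the unadjusted SE is the planned one.

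**4. What a loss beyond plan would need.** PPE variance would have to come on top of the planned total. An extra 0.1, 0.2 or 0.4 of the total raises the SE to 0.233, 0.252 or 0.283 × SD. At SD 12 the middle case gives 0.252×12 = 3.02 min and 91% power. The protocol gives no figure that supports any such addition.

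**The case against.** The strongest reply is that the sentence is the ordinary rationale for a crossover. The sentence before it makes alternation conditional on a further proning session, and the sentence itself speaks of differences between patients, not changes within one. That is fair as to intent. But it names PPE need as an example and sets no limit for single-session patients, whom the protocol itself expects to be a third.

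It can also be said that leaving prognostic covariates out of a crossover model is not an error, and that the free-text delay and comment fields in Table 2 may catch PPE. The first point stands, which is why this is an improvement and not a fault in validity. The second stands only in part, because free text is not a systematic record.

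Two stronger readings are tempting, and the documents do not support them.

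- **That the trial will be less precise than planned.** The dropout, the 0.3 between-treatment correlation and the absence of any mentioned covariate are all in the power assumptions. A change in PPE between sessions would sit in the 40% of variance left at patient-by-method level. No passage says that PPE status changes or by how much it lengthens a turn; the day 1 and day 5 example only shows how alternation resumes. The stated power also concerns repositioning time, so there is no planned precision for staff time to fall short of.
- **That one-session patients bias the estimate.** With 5 per method and 40% prevalence, a PPE imbalance of at least 2 of 5 arises in about 33% of trials. At 15 min it moves the estimate by 0.134×0.4×15 = 0.8 min. That is chance imbalance under randomisation, already inside the SE.

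**Conclusion.** The point holds as an overstatement of what alternation achieves and as a missed, inexpensive gain. It does not hold as a loss of planned precision or as bias.

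For BMI the gain is about 0 to 2% of the variance of the method effect. For PPE it is about 0 to 20% over nearly all of the assumed range, and about a third only when a 15 min effect meets one in five patients changing status. These figures rest on an assumed SD of 12 min, 40% PPE prevalence, and PPE effects and change rates that the protocol does not give. They also assume an analysis whose random effects match the 0.7 and 0.3 correlations. The wording point rests on none of these.

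**What to change.** 1. Add BMI as a fixed effect in the repositioning-time model. Height and weight are already in Table 4 and are needed to apply the exclusion limits.
2. Add one PPE yes/no item to Table 2 and include PPE in use at that turn as a covariate. Give it a not-recorded category, so that turns entered before the change are not dropped under the no-imputation rule. Report the model without PPE alongside, because PPE is observed after randomisation and is missing for early turns.
3. Limit the Study procedures sentence to factors that stay constant, in patients who receive both methods.

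**Cost.** One extra item on an existing form, about three degrees of freedom (BMI, PPE, not recorded), and approval of the amended documents. No extra patients are needed. Recruitment began in May 2025, so PPE status will be missing for turns already recorded, and the gain falls the later the item is added. The sections on refusal or withdrawal of consent and on source data restrict patients who decline or die to primary-outcome data. Keeping height and weight for them must be reconciled with those sections.
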